## Methods/Design

### Study design

This is an 18-month, community-based, cluster randomised controlled trial in which older adults residing in retirement villages, who are at increased risk of falling, will be randomly allocated to: 1) an exercise programme involving dual-task functional power training (DT-FPT), or 2) a usual care control group. The intervention is divided into 3 distinct phases: 6 months of supervised and structured DT-FPT, a 6-month ‘step down’ maintenance programme, and a 6-month follow-up. Multi-care level retirement villages will be recruited but only people that live independently in apartments or units, but share common-room facilities, will be recruited. The trial is managed by the Centre for Physical Activity and Nutrition Research at Deakin University, Burwood, Melbourne, Australia and is funded by a National Health and Medical Research Council (NHMRC) Project Grant (ID1046267). The study has been approved by the Deakin University Human Research Ethics Committee (HREC 2013-051), and is registered with the Australian and New Zealand Clinical Trials Registry (ACTRN12613001161718). Written informed consent will be obtained from all participants prior to commencement of the trial.

### Participants

A total of 280 men and women aged 65 years and over at an increased risk of falling (see below and Table 1) and who currently reside in retirement villages will be invited to participate in this study.

**Table 1 Tab1:** **Falls and fracture risk questionnaire for inclusion into the trial**

**Risk factor**	**Guidelines**	**Score (circle)**
History of falling^a^	Self-reported risk of falling (1 or more falls in past year)^a^	3
Age	>75 years	2
	70 to 75 years	1
Low trauma fracture^b^ or osteoporosis	Since age of 50 years (T-score < −2.5 SD at the hip or spine)	2
Difficulty when rising from a chair or toilet without using arms	When getting up from a chair or the toilet do you use your arms?	2
History of slipping or tripping	Have you had a slip or trip in the past year?	2
Medication use	How many medications are you currently taking? If four or more include as two points	2
Use of walking aid	Yes or No?	2
One psychoactive drug	Do you take any medications to treat anxiety, panic attacks or insomnia seizures?	1
On feet < 4 hours per day	Are you on your feet < 4 hours a day?	1
Multi-focal glasses	Do you wear multi-focal glasses?	1
Poor vision (for example, cataract, glaucoma)	Self-reported or assessed by primary care physician - Do you have cataract or glaucoma?	1
When walking	Do you ever have trouble walking or feeling unsteady on your feet?	1
Self-rated health as fair or worse compared to last year	Excellent/Good/Fair/Poor/Very poor (very poor = 1 point)	1
Thinness	Body mass index (BMI) < 20	1
High risk of vitamin D deficiency	In summer, ‘Do you spend < 10 minutes per day outdoors (with part of your body exposed to sunlight), without taking vitamin D supplements between the hours of 10am to 3 pm’?	1
	OR	
	In winter, ‘Do you spend < 30 minutes per day outdoors (with part of your body exposed to sunlight), without taking vitamin D supplements’?	
Total score (Include if score ≥ 3)**:**		

^a^A fall is defined as an event that results in unintentionally coming to rest on the ground or a lower surface, other than as a consequence of a sudden onset of paralysis, epileptic seizure, or overwhelming external force.

^b^A low trauma fracture is defined as a fragility fracture of the spine, hip or wrist.

#### Recruitment

Retirement villages within the Melbourne metropolitan region and surrounding areas in Victoria, Australia will be approached via mail or telephone and invited to participate in the study. For those that agree and consent to participate, the manager will be asked to provide a single numbered list of residents aged 65 years and over who will receive an invitation letter to participate in the study. Advertisements will also be placed in village newsletters and on relevant notice boards, and information sessions will be conducted by the research staff at each village. While the total number of villages recruited will depend on the size of each village (number of residents), the goal is to recruit between 15 to 20 people per village. All participants who express an interest in the study will be required to undergo screening to determine their eligibility to participate in the trial as outlined below. To maximise recruitment, permission will also be sought from each retirement village to invite non-residents aged 65 years and over who fulfil the inclusion criteria to participate in the trial. These participants will be recruited via doctor/health professional referrals, a local media campaign and advertisements placed on relevant notice boards and word of mouth.

#### Screening and eligibility

All interested participants will be screened over the telephone and will be eligible for the study if they score ≥ 3 points on an algorithm adapted from identified risk factors for falls (Table 1). In addition, participants must be able to speak English proficiently, walk unaided or with minimal assistance (walking stick or walker) for at least 50 meters and be cognitively intact (score ≤ 2 errors on the Short Portable Mental State questionnaire) [48]. All eligible participants will then be screened with the Exercise and Sports Science Australia (ESSA) exercise screening tool to evaluate any contraindicated medical conditions to exercise. Participants answering ‘yes’ to any of these screening questions will be required to obtain medical clearance from their local doctor prior to participating in the intervention. For all other participants, an information letter outlining the study aims and its requirements will be sent to their doctor to inform them that their patient is participating in this research trial.

Participants will be ineligible based on the following criteria: 1) current or prior participation in a structured progressive resistance training (PRT) programme and/or organised balance training more than once per week in the past 3 months; 2) acute or terminal illness likely to compromise exercise participation; 3) unstable or ongoing cardiovascular/respiratory disorders; 4) musculoskeletal or neurological diseases disrupting voluntary movement or that might limit training; 5) upper or lower extremity fracture in the past 3 months, or 6) visual impairment not corrected with glasses. To assess for possible response bias, data on the age and sex for all eligible non-participants residing at each retirement village where the study will be conducted will be collected.

#### Randomisation

Randomisation will be performed by cluster (village) to avoid any potential contamination and facilitate logistical arrangement. Each village will be given an ID number and group assignment by blocks of 2, stratified by village size (<75 or ≥ 75 residents), will be performed by a researcher not involved in the study using computer-generated random numbers (Microsoft Excel, Microsoft Corp., Redmond, WA, USA). A flow diagram of the study protocol is outlined in Figure 1.

**Figure 1 Fig1:**
[figure not shown]
**Flow diagram of the progress from screening to the final follow**-**up assessment.**

#### Allocation concealment and blinding

Retirement villages will be allocated to the intervention or usual care only after all participants have completed baseline testing. The retirement villages, the residents and the research staff undertaking the baseline testing will be blinded to the allocation until this point. It is difficult for the participants within the exercise intervention to be blind in trials of exercise, as well as for all research staff to be blind to the allocation of the participants as they will often recruit participants and undertake baseline and follow-up assessments. Thus, for pragmatic reasons not all research staff will be blinded in this study. However, research staff undertaking the baseline and follow-up assessments and the statistical analysis will be blinded to the treatment allocation of the retirement villages.

### Intervention

#### Dual-task functional power training

Participants residing in the villages assigned to the DT-FPT programme will be asked to train twice a week for 26 weeks. All training will be conducted on-site at each retirement village in small groups (8 to 10 per group), and will be implemented and supervised by accredited exercise physiologists (AEPs), physiotherapists or experienced Certificate IV personal trainers. All trainers involved in the study will be required to attend a ‘train-the-trainers’ workshop and will be provided with a detailed instructor manual that will contain all the necessary information to implement the exercise programme. The delivery of the programme will be standardised through regular quality assurance visits and monthly trainer meetings with the research staff.

The 26-week programme will be divided into an initial 2-week familiarisation (orientation) period, followed by 3 distinct but interrelated 8-week phases termed ‘mesocycles’. Each mesocycle will be further divided into 2-week achievable microcycles that are designed to be progressively more challenging. Each training session is designed to be completed within 45 to 60 minutes and will be divided into 4 components: 1) a warm-up consisting of rhythmic and range of motion exercises, 2) challenging balance and mobility activities, 3) HV-FPT, and 4) a cool-down. Dual-task activities will be incorporated into the challenging balance/mobility and HV-FPT. All programmes will be individualised to the functional capabilities of each participant based on their initial assessment.

For the challenging balance and mobility training, participants will be asked to engage in a range of activities designed to simulate common daily functional tasks such as avoiding and stepping over obstacles, weight-shifts and leaning to reach objects. Particular emphasis will be placed on training the lower limb muscles (ankle dorsi- and plantar-flexors, knee flexors and extensors, hip abductors, adductors and extensors) that are associated with balance and mobility. The programme will become progressively more challenging through the inclusion of more difficult postures with a gradual reduction in the base of support, dynamic movements that increasingly perturb the centre of gravity, reducing sensory input, negotiating different environmental hazards and the use of dual-task activities. For each session, participants will be required to perform at least two challenging balance or mobility exercises.

For the HV-FPT component, the goal will be to increase lower limb muscle power, movement speed, force and mobility. Participants will be instructed to perform a series of resistance and functional tasks where all repetitions for each concentric (shortening) phase of the exercise will be performed as quickly as possible, while the eccentric (lengthening) phase of the exercise action will be controlled over 3 to 4 seconds. The exercises will become progressively more challenging by increasing the resistance, difficulty or changing the exercise to another more complex task. Core exercises will include: multi-directional rapid stepping and bench stepping, combined with functionally relevant resistance exercises (squats, hip abduction, hip extension and ankle plantar- and dorsi-flexion). Weighted vests, thera-bands, tubing, hand-held weights and sand bags will be used to increase the training loads. Participants will perform 2 sets of 10 to 20 repetitions progressing to 50 repetitions for the stepping exercises. For the functional resistance exercises, participants will perform 2 sets of 10 to 15 repetitions at an intensity of 4 to 6 (moderate to hard) on the 10-point Borg’s Rating of Perceived Exertion scale [49], and resistance will be increased as tolerated using this scale.

The dual-task training will incorporate a combination of cognitive and secondary motor tasks that will be performed simultaneously whilst undertaking the challenging balance/mobility and HV-FPT. Prior to incorporating the secondary tasks into the programme, participants will undertake at least 2 weeks of training without this component to ensure safety and confidence with the single-task exercises. Cognitive and motor tasks will then be progressively incorporated into the programme. Examples of cognitive tasks that may be incorporated into the programme include: tasks related to verbal fluency (for example, listing words within a category (names of animals, vegetables, fruit, and so on) or by letter (a word that begins with ‘D’)), serial subtraction (for example, subtracting three from a given start number) and information processing (for example, stepping rapidly in a given sequence on command or from memory) onto thin slip-resistant mats or discs that may be different in colour. Dual tasks will be progressed or changed on an individual basis every 4 weeks or as needed.

To maximise social interaction and enjoyment and enhance adoption and maintenance, participants will train in small groups (8 to 10 per group) and we will incorporate established behavioural models that have previously been successful in older adults. Effective strategies have included: social support (buddy system); regular feedback (fitness testing); positive reinforcement through rewards (T-shirts, caps) and public recognition in newsletters for attendance and adherence; and ongoing education via fact sheets and newsletters.

#### Usual care control group

Participants residing in the villages assigned to the control group will receive their usual care from their medical practitioner and community services. They will also be encouraged to adhere to the current guidelines of at least 150 minutes per week of moderate intensity physical activity. They will also receive standardised falls prevention and physical activity advice in the form of booklets (Department of Health: ‘*Don’t fall for it - falls can be prevented’*, and *‘An active way to better health’*) along with generic project newsletters that contain project updates to help minimise attrition over the 18-month duration. There is no evidence that the provision of written falls prevention or physical activity advice alone reduces falls risk [50].

#### ‘Step down’ maintenance programme and follow-up

A 6-month ‘step down’ maintenance programme will be introduced after the supervised training for the intervention group since previous trials have shown that the benefits of exercise on falls incidence are largely lost after programme cessation [46,47]. The ‘step down’ represents a decrease in the level of free supervised training that will be offered to the participants by the exercise staff who delivered the first 6-months of the programme. Prior to this phase we will liaise with all village managers to discuss strategies as to how they can continue to offer the programme within their village without the intensive intervention of the research staff. Village managers will be provided with a number of potential options as to how they can continue to offer the programme to the residents. To facilitate this transition, participants will be offered 1 weekly 1-hour exercise class led by our trained exercise staff who have completed our ‘train-the-trainers’ workshop. In addition, since one of the goals of the main intervention is to improve gait and muscle function under dual-task conditions, participants will also be encouraged to undertake at least one brisk walking session per week. Within each village, staff/participants will be encouraged to form walking groups. Compliance with the ‘step down’ programme will be monitored by attendance sheets completed by the staff at each village and a diary for recording the walking. After the 6-month ‘step down’ programme, participants will be followed for a further 6 months to establish the long-term residual effects on falls. Participants and staff at the villages will not receive any support or advice during this final 6-month follow-up.

### Outcome measures

A summary of the outcome measures is shown in Table 2. Participants will attend 4 testing sessions at their retirement village throughout the study (baseline, 6, 12, and 18 months).

**Table 2 Tab2:** **Summary of the outcome measures**

**Outcome measures**	**Data collection method**	**Data collection points**			
		**Baseline**	**6 months**	**12 months**	**18 months**
Primary outcome measure					
Falls	Monthly falls calendars	Monthly			
Secondary outcome measures					
Muscle power	5-consective sit-to-stands	x	x	x	x
Muscle strength	30-second Sit-to-Stand test	x	x	x	x
	Isometric knee extensor strength	x	x	x	x
	Isometric dorsi-flexion strength	x	x	x	x
	Hand grip dynamometer	x	x	x	x
Muscle function and balance	Timed up-and-Go: single- and dual-task	x	x	x	x
	Four-squared step test	x	x	x	x
	Choice reaction time	x	x	x	x
Single- and dual-task gait	Gait (4.9 m electronic walkway): gait velocity, cadence, step length, double support time, stride wide and dual-task cost	x	x	x	x
Instrumental Activities of Daily	Lawton IADL questionnaire	x	x	x	x
Living (IADL)					
Health-related Quality of Life	Short Form (36) version 2 questionnaire and the Assessment of Quality of Life - 6D scale	x	x	x	x
Cognitive function	CogState Brief Battery computerised tests	x	x	x	x
Falls self-efficacy	Falls Efficacy Scale-International questionnaire	x	x	x	X
Additional measures					
Anthropometry	Height, weight and body mass index	x	x	x	x
Body composition	Bioelectrical impedance (fat mass, fat-free mass and % fat)	x	x	x	x
Physical activity	Community Healthy Activities Model Programme for Seniors questionnaire	x	x	x	x
Falls-related injuries	Monthly calendar	Monthly			
Health and medical history	Lifestyle questionnaire	x	x	x	x
Dietary intake	Anti-Cancer Council Food Frequency Questionnaire	x	x	x	x
Adverse events^a^	Questionnaire and interview		x	x	x
Exercise programme compliance	Calculated from exercise cards	Collected every month			

^a^Adverse events will also be collected at 3 months.

### Primary outcome measures

The primary outcome will be the number of falls over the 6-, 12-, and 18-month period. The initial comparison of falls outcome between the two groups will be analysed according to the number of falls per person year and the proportion sustaining one or more falls. Subsequent analyses will allow for the non-independence of multiple events for the same participants. Participants will record all falls ((F (fall) or N (no fall)) each day on a monthly falls and adverse events calendar, which will be returned monthly via postage-paid mail. Any participants who do not return the monthly falls calendar will be contacted by telephone by the research staff. When a fall is recorded, a research staff member will administer a standardised questionnaire via telephone to record more specific details of the fall location, cause, injury, treatment and the healthcare utilisation. The fall event data will be coded using the International Classification of Diseases, 10th edition (ICD-10).

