**Methods/Design:**

The study design is an 18-month cluster randomised controlled trial in which 280 adults aged ≥65 years residing in retirement villages, who are at increased risk of falling, will be randomly allocated to: 1) an exercise programme involving DT-FPT, or 2) a usual care control group. The intervention is divided into 3 distinct phases: 6 months of supervised DT-FPT, a 6-month ‘step down’ maintenance programme, and a 6-month follow-up. The primary outcome will be the number of falls after 6, 12 and 18 months. Secondary outcomes will include: lower extremity muscle power and strength, grip strength, functional assessments of gait, reaction time and dynamic balance under single- and dual-task conditions, activities of daily living, quality of life, cognitive function and falls-related self-efficacy. We will also evaluate the cost-effectiveness of the programme for preventing falls.

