
The primary aim of this community-based, cluster randomised controlled trial is to evaluate whether dual-task functional power training (DT-FPT) can reduce the rate of falls in community-dwelling older adults at increased risk of falling. Secondary aims of the study are to:Determine if DT-FPT can improve lower extremity muscle power, balance and gait under single and dual-task simulated ‘*real-life’* conditions.Evaluate the effects of DT-FPT on health-related quality of life (HR-QoL), falls-related self-efficacy and cognitive function.Evaluate the efficacy of a ‘step down’ maintenance programme on falls risk.Determine the cost-effectiveness of DT-FPT and the ‘step down’ maintenance programme for preventing falls. The results will be expressed as the incremental cost of the intervention in monetary terms per unit gain per fall averted.

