### Sample size

Based on previous research in Australia [71-73], we anticipate that approximately 45% of the usual care control group will experience a fall throughout the study. To detect a 40% reduction in the rate of falls (for example, from 45% to 27%) in the DT-FPT group, we estimate that we will require 118 participants per group (2-tailed, *P* < 0.05 and power of 0.8). This allows for a 15% loss to follow-up due to death or withdrawal from the study. To account for cluster randomisation, we will assume a conservative intra-cluster correlation coefficient of 0.01 [74], giving a design effect of 1.19, assuming approximately 15 to 20 participants are recruited per village. This gives a sample size of 140 per group (280 participants from approximately 15 villages). This sample size will also provide sufficient power (0.9, 2-tailed, *P* < 0.05) to detect significant and clinically meaningful differences in many of the secondary outcome measures. Previous research has shown that 6 months of high-velocity resistance training in older adults can result in a 50% increase in peak muscle power (SD 18%) [20]. This mode of training has also resulted in a reduction in chair rise time of approximately 11% (SD 12%) and stair climbing time of approximately 7% (SD 10%) [20,21]. For the usual care control group, we estimate a mean change of 0 (SD 10%). Thus, to achieve 90% power at *P* < 0.05 (2-tailed), we estimate that 46 participants per group would be required to demonstrate between group differences of this magnitude in these measures. We will also have sufficient numbers to detect the smallest clinically significant differences in other measures of function and the SF-36. Perera *et al*. [75] calculated that a small meaningful change (difference) in function is around 5% (0.05 m/s gait speed) and a substantial change is around 10% (0.10 m/s gait speed). Since we will recruit a cohort at increased risk of falling, we anticipate greater changes based on previous work in healthy community-dwelling older adults (gait speed +7%, chair rise +13%) [21]. We estimate that 32 to 42 participants per group will be needed for a statistical power of 0.9 (2-tailed, *P* < 0.05) to detect differences between the groups of 14 to 25% in gait speed and chair rising time. Using data from a pilot study on dual-task stepping exercise [45], we estimate that we will need 48 participants per group to detect a 20% difference (SD 25%) in dual-task cost at 90% power (2-tailed, *P* < 0.05). For the sub-scales of the SF-36, we anticipate a change of 10 points in the DT + FPT groups with a small age-related change (decrease) in the controls. In various patient groups a 5 to 10% change is regarded as the minimal important difference. We note that the effects of resistance training on SF-36 are mixed, but differences of 15 to 52 points for the various sub-scales have been reported [76].

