
### Statistical methods

Primary analyses will be conducted on an intention-to-treat basis using STATA statistical software release (STATA, College Station, TX, USA). Per protocol analysis will also be performed by including all participants who are at least 80% compliant to the exercise (as measured by the number of exercise sessions attended). Initially, descriptive statistics will be computed to compare the intervention and control groups on background variables and baseline measures. Imbalances on prognostic factors between the groups will be adjusted for during analyses. Calculation of QoL scores (SF-36 v2, AQol-6D) will utilise published ‘weightings’ most relevant to this population. Baseline measures and changes in outcome variables over the study period for each study arm will be presented as means (± SD) with 95% confidence intervals. The effect of the intervention on the primary outcome variables will be assessed using negative binomial regression, to account for the non-independence of multiple events for the same participants and to allow for over-dispersion [77]. To account for clustering, the negative binomial regression analysis will be carried out using the generalised linear mixed modelling approach, with observations clustered within retirement villages; village will be modelled as a random effect. Differences between the intervention and control groups on the secondary outcome measures will be examined using linear mixed models with assessment times clustered within individuals and individuals clustered within villages. Village and, where appropriate (as determined by the likelihood ratio tests) individuals, will be modelled as random effects. The secondary outcome variables will be checked for normality prior to analysis and transformed appropriately if necessary. For both primary and secondary outcomes, random effects will be computed utilising robust standard errors. For all outcomes, primary analyses will compare unadjusted differences between the study groups at each follow-up. Supplementary adjusted analyses, with adjustment for potential covariates (baseline values of relevant outcome, age, sex, use of medication, chronic conditions, falls history and other background variables that show imbalances between the intervention and control groups) will also be conducted.

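### Falls at 6, 12 and 18 months are all named primary with no ranking, which raises the false-positive risk to about 8 to 11% if each is tested at 5% and leaves the step-down and residual-effect questions without a matching analysis

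*Protocol article*

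**What the plan says.** The abstract states: "The primary outcome will be the number of falls after 6, 12 and 18 months". The section on primary outcome measures repeats this as "The primary outcome will be the number of falls over the 6-, 12-, and 18-month period". Neither place puts one time point ahead of the others.

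The same section says that the first comparison of the groups will be "analysed according to the number of falls per person year and the proportion sustaining one or more falls", and then: "Subsequent analyses will allow for the non-independence of multiple events for the same participants".

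Under Statistical methods, "The effect of the intervention on the primary outcome variables will be assessed using negative binomial regression", fitted as a mixed model with village as a random effect. That section adds: "For all outcomes, primary analyses will compare unadjusted differences between the study groups at each follow-up".

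The Sample size section assumes that 45% of controls fall during the study, against 27% with DT-FPT, and says: "we estimate that we will require 118 participants per group (2-tailed, *P* < 0.05 and power of 0.8". This is a single comparison, and the Study design section gives the study length as 18 months.

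Two further questions concern the later phases. A secondary aim at the end of the Background is the efficacy of the step-down "maintenance programme on falls risk". The section on the step-down programme and follow-up says that the last six months are there to establish the residual effect on falls.

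**The concern.** A confirmatory trial sized for one 5% test needs one result that decides it, or a stated order of results. Here three results have equal standing. If they disagree, for example a clear effect at 6 months and none at 18, the text does not say whether the trial succeeded, and a favourable time point could be chosen afterwards.

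The second difficulty is what the later time points measure. The three six-month phases differ: supervised training, reduced supervision, then no support. A count from baseline to 12 or 18 months mixes them. The article asks about the second and third phases separately, but the outcome as worded does not isolate either.

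**Working it through.** **Plan's own figures.** The article gives no overall error rate for the three time points. Its only relevant figures are for the single sized comparison.
- Two-proportion formula, pooled, 0.45 v 0.27, mean 0.36: n = [1.96√(2×0.36×0.64) + 0.842√(0.45×0.55 + 0.27×0.73)]² / 0.18² = (1.331 + 0.561)² / 0.0324, which rounds up to 111 per group. Dividing by 0.85 for loss gives 131, not the stated 118. That mismatch is a separate matter and does not affect this point.
- Clustering step: 118 × 1.19 = 140.4, which reproduces 140 per group.

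**Chance of at least one false positive over three counts from baseline.** Assumptions, none of them stated in the article:
- each test is two-sided at 5%;
- all counts start at baseline;
- falls are gamma-Poisson with over-dispersion k from 0 to 3 and a constant rate;
- the mean m per six months is set so that 45% have fallen by 18 months: (1 + 3km)^(−1/k) = 0.55, or exp(−3m) = 0.55 when k = 0;
- village clustering is left out.

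For counts over i and j six-month periods (i < j), the covariance is im + k·i·j·m² and the variance over i periods is im + k·i²·m². The correlation is therefore

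(im + k·i·j·m²) / √[(im + k·i²·m²)(jm + k·j²·m²)],

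which is √(i/j) when k = 0. A trivariate normal with these correlations gives:

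| k | m | r(6,12) | r(6,18) | r(12,18) | P(at least one P < 0.05) |
|---|---|---|---|---|---|
| 0 | 0.199 | 0.707 | 0.577 | 0.816 | 10.7% |
| 0.5 | 0.232 | 0.743 | 0.635 | 0.854 | 10.3% |
| 1 | 0.273 | 0.779 | 0.690 | 0.886 | 9.8% |
| 2 | 0.384 | 0.847 | 0.789 | 0.932 | 8.9% |
| 3 | 0.557 | 0.902 | 0.866 | 0.961 | 8.0% |

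Simulation with 119 per arm (140 × 0.85) agrees, at about 8 to 11%. Adding the proportion of fallers at each time, six tests in all, gives about 15% at every k.

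**What the later counts show.** Take equal control rates in each period and illustrative period rate ratios of 0.6, 0.8 and 1.0:
- 0-6 months: 0.60
- 0-12 months: (0.6 + 0.8)/2 = 0.70
- 0-18 months: (0.6 + 0.8 + 1.0)/3 = 0.80

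No effect at all in months 13-18 would still be reported as a 20% reduction at 18 months.

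**The case against.** Several points on the other side are fair.

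- *Multiplicity may be handled in the analysis plan.* That plan is not shown, and the 5% level appears only in the Sample size section. Testing each time point at 5% is therefore an assumption, and the lack of an adjustment method is not the finding. What remains is that the article itself names three time points as primary and ranks none.
- *Counts from baseline are inferred.* The wording on follow-ups could mean separate six-month windows. The later phases would then be isolated, but three separate windows each tested at 5% give about 12 to 14% under the same assumptions. The ambiguity needs settling either way.
- *Six primary tests.* A reader might infer that the rate and the proportion of fallers are co-primary at each time, giving about 15%. The article does not say so. The primary aim concerns the rate of falls, the statistical section gives the primary outcome one method, and the proportion appears only in an initial comparison. Its status is unclear, so 15% is a conditional upper figure.
- *A conflict between sections.* A reader might infer that the initial comparison ignores repeat falls and so contradicts the negative binomial model. The text describes a sequence: a first comparison, then analyses that allow for repeat falls, which the statistical section specifies. No naive Poisson test is planned, so an error rate for one would not describe this trial.
- *Waning would be hidden.* This is too strong. In the example the ratios visibly shrink, and falls are recorded daily, so rates for each window can be obtained. The point is only that the cumulative results do not themselves estimate the later periods.
- *Step-down and carry-over.* The step-down is offered to the intervention group with no second randomisation, so its own effect cannot be separated from carry-over. That is a limit of the design and bears on wording, not on the choice of primary endpoint.

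**Conclusion.** The point holds in this form. Three time points are primary without an order, while the trial is sized for one two-sided 5% comparison over 18 months. With each tested at 5% on counts from baseline, the overall false-positive risk is about 8 to 11%. The higher end applies with little over-dispersion, and the lower end with the stronger over-dispersion that the choice of model allows for. The figure depends on the assumed level, windows and dispersion; the article supplies none of them for these tests. On the same reading, the 12- and 18-month results do not answer the step-down aim or the residual-effect question. The data needed are being collected, so the defect lies in what is named and how it will be analysed.

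**What to change.** Recruitment has started, so make these changes before any outcome comparison is seen.

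1. Name one primary time point for the rate ratio from the negative binomial mixed model, or state a fixed testing sequence. Eighteen months matches the period used for sizing, but the sizing is of a proportion, so the form of the endpoint would still differ and this should be acknowledged.
2. Make the other time points and the proportion of fallers secondary, and label the initial comparison descriptive.
3. State whether each count runs from baseline.
4. Estimate months 0-6, 7-12 and 13-18 as separate windows with a group-by-period term. Report the 7-12 month result as DT-FPT followed by step-down versus usual care.

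The cost is protocol and registry wording and one further model, with no new data. Only one time point, or the first in the sequence, leads the confirmatory claim, and window estimates are less precise than cumulative ones. Keeping all three as primary with a Bonferroni split costs far more. On the article's proportions, 0.05/3 needs 148 evaluable per group, or 175 with 15% loss, or about 208 with the design effect (148/0.85 × 1.19 = 207.2; rounding up the unclustered figure first gives 175 × 1.19 = 208.3), against 140 planned.
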